#### 2. Gross Motor Function Measure (GMFM-88)

The 88-item version of the GMFM includes five dimensions (Prone and Supine; Sitting; Crawling and Kneeling; Standing; Walking, Running and Jumping). Each item is measured by observation and scored on a 4-point ordinal scale. The GMFM is the gold-standard measure used in clinical trials for children with cerebral palsy. Validation of the GMFM for children with cerebral palsy was first published in 1989 [68]. Additional evidence of validity and responsiveness of the GMFM for children with spastic diplegia and quadriplegia has also been established [69]. Several studies have documented the test-retest and inter-rater reliability of the 88-item GMFM [69-71]. Inter-rater reliability ranges from 0.87 to 0.99 and test-retest reliability ranges between 0.76 to 0.99

### Participation

#### 1. Pediatric Quality of Life Inventory ~ PedsQL 3.0 Cerebral Palsy Module

The PedsQL 3.0 CP Module was designed to measure HRQoL dimensions specific to CP [72]. The CP Module is divided into two components: parent report for toddlers aged 2–4 years; and a child self-report and parent report of children aged 5–7, 8–12 and 13–18 years old. The parent report for toddlers contains 22 items. These 22 items are split into 5 dimensions comprised of daily activities, movement and balance, pain and hurt, fatigue and eating activities. Psychometric properties for the PedsQL 3.0 CP Module were derived from a study with a sample of children with Cerebral Palsy ages 5–18 years [72]. Construct validity was supported for the CP Module and a reliability of was reached at 0.79 for child report and 0.91 for parent report using Cronbach's alpha [72].

#### 2. Children's Assessment of Participation and Enjoyment (CAPE)

The CAPE is a measure developed at *CanChild *for a study of children's participation and is designed to assess children's participation in voluntary, day-to-day activities outside of mandated school activities [73]. The CAPE uses pictures to help children identify what activities they do. For each identified activity they are asked several questions: how often they have done the activity in the past 4 months, with whom they typically do the activity; where they do the activity and how much they enjoy the activity. This measure has been used successfully with over 400 children in the "Participate" study. Test-retest reliability of the CAPE scales ranges from 0.80 – 0.90. Scores on the CAPE correlate significantly with child's communication, social and physical function.

### Environment

#### 1. Family Empowerment Scale (FES)

Koren, DeChillo and Friesen [74] designed the Family Empowerment Scale (FES) to measure this construct. Singh et al. [75] performed a factor analysis on the FES revealing four dimensions: systems advocacy, knowledge, competence and self-efficacy. The FES has been used in a number of efficacy studies in the fields of children's mental health [76,77], diabetes (Florian & Elad, 1998), and low-income families [78]. The FES has excellent reliability (Internal consistency 0.87 – 0.88; test-retest reliability 0.77–0.85) and evidence of discriminative validity.

#### 2. Measure of Processes of Caregiving (MPOC-20)

MPOC was developed to measure the processes of professional caregiving [79]. MPOC is a 20-item questionnaire with five constructs 1) Enabling & Partnerships; 2) Providing General Information; 3) Providing Specific Information about Child; 4) Coordinated and Comprehensive Care for the child and family; 5) Respectful and Supportive Care. MPOC has been used in a study of factors affecting the health of caregivers of children with disabilities [80]. Internal consistency was examined using 3 data sets with Cronbach's alpha ranging from 0.81–0.96. Test-retest reliability (n = 29) had ICC values ranging from 0.78–0.88 [81]. Reliability and validity of the MPOC are excellent.

### Analyses

All data will be stored in a secure environment and analysed at the McMaster coordinating site. Data from each outcome assessment will be collected and summarized for each treatment group. Descriptive statistics including frequencies, means, and standard deviations will be calculated. To test for the effect of the intervention, the differences between the means for the task/context-focused group and the regular therapy care group will be evaluated. The primary analysis will be to estimate the differences in the change scores between groups, comparing baseline to both the 6-month intervention and 3-month follow-up intervals. A combined analysis for the 3 time points will use a mixed effects repeated measures analysis of variance (ANOVA) linear model. Treatment groups and time will be taken as fixed factors, while the clusters (therapists) will be regarded as a random factor nested within treatment groups [82].

We anticipate that the sample sizes will be approximately balanced between the intervention groups, but if unequal sample sizes occur for some reason, generalized least squares techniques will be used for the statistical analysis. The primary focus will be on the group × time interaction, for which the cluster × time interaction will be used as an error term for testing significance. The statistical significance level will be set at 0.05 for the primary outcome (PEDI assessment). Results will be presented in terms of the estimated mean difference in change between the treatment groups, together with 95% confidence intervals. For secondary outcomes, we will again report means and confidence intervals, but we will be more cautious in our interpretation of these results, recognizing that a large number of statistical comparisons will be made, and also that our power for secondary outcomes may not be as great as for PEDI. Prognostic variables such as age, center and co-intervention, if shown to be important predictors of outcome, will be included in the analysis as covariates. Statistically significant interactions would imply that the treatment effects differ between age and/or severity subgroups. If such interactions are significant, individual contrasts will be examined to determine if there are age/severity subgroups in which treatment differences are statistically and clinically important. An intention to treat analysis will be employed – those who do not adhere to treatment (miss >20% of sessions) will be included in the analysis in their original group. Children who drop out of the study will be included in the analysis in their original group if outcome data can be collected.

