### Sample size

Sample size was calculated for the primary study outcome, using the following: where n = number of subjects per group, **α **= significance level (2-sided testing), **1 - β **= power, **σ **= SD of change within individuals, ICC = intraclass correlation, m = average cluster size, **Δ **= minimum absolute change to be detected, number of clusters (therapists) = n/m. The within-child standard deviation for change on the PEDI scale was set at 7. This value is based on data reported in the PEDI manual, and data from Ketelaar et al. [33]. Specifically, the value 7 is the working average of the within-child standard deviation observed by Ketelaar et al. [33] for self-care functional skills and mobility. We took the average cluster (number of children per therapist) size to be 3, the ICC to be 0.1, and therefore assumed a variance inflation factor (design effect) associated with therapists to be 1.2. The variance inflation factor allows for the possibility that some therapists may be more effective in inducing a change on the PEDI scale compared to other therapists, and takes into account the clustered nature of the sample of participating children. Based on data from our task/context-focused pilot study, we projected an estimated difference in the change scores between the treatment groups of 3 points on the PEDI, and used a two -sided α-value of 0.05, with power of 80%. Our sample size estimates are based on the PEDI because it demonstrates the greatest score variability, and because it is the primary measure of interest in the study. The specifications above lead to a required sample size of 104 children per group, which we rounded to 105 per group so that 35 therapists would be required per group. With additional children to account for dropouts, our target sample size is set at 220.

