### Recruitment procedure

Each center in the study has a site coordinator who contacts all therapists to inform them about the study and to obtain their consent to participate. Once therapists have consented to participate in the study they will be block randomized by the coordinating site (by OT or PT discipline) into either treatment arm. On behalf of the research team, each center in the study will mail information that will describe the study to eligible families. Families will be asked to read over the information and indicate their interest in the study on a form to be returned to the research center in a stamped self-addressed envelope. At the baseline visit, study assessors will review the information sheet with the families and witness and co-sign the consent form. Assessors will leave a signed (carbon) copy of the consent form with the family.

Children from consenting families will follow their therapist into the treatment arm that the therapist was randomly assigned to. Due to the nature of the therapy, it will not be possible to keep therapists or parents unaware of the child's treatment group. Therefore, trained, reliable evaluators who are blinded to group assignment will measure all outcomes. Evaluations will be completed at baseline, after 6 months, and at a 3-month follow-up.

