#### 2. Gross Motor Function Classification System (GMFCS)

The Gross Motor Function Classification System (GMFCS) [66] will be used to classify the gross motor function of children and stratify children based on severity (less severe, levels I and II; more severe, levels III-V). The GMFCS has evidence of very good reliability and validity.

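### Adjustment for baseline variables depends on an undefined importance rule; baseline PEDI, age, GMFCS stratum and therapist discipline should be fixed covariates in the primary model

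*Protocol article*

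**What the plan says.** The Analyses section makes the difference between groups in change score the primary comparison, from baseline to 6 months and to the follow-up three months later. It adds a combined repeated-measures model over the three time points, in which "Treatment groups and time will be taken as fixed factors" and therapists are random within treatment group. The focus is the group × time interaction, tested against cluster × time.

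Covariates are handled by a conditional rule: "Prognostic variables such as age, center and co-intervention, if shown to be important predictors of outcome", are to be included. The section does not define important. Severity comes in afterwards, through interactions and contrasts in age and severity subgroups.

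Two other sections bear on this. The GMFCS section says the classification will be used to "stratify children based on severity (less severe, levels I and II; more severe, levels III-V"). The Recruitment procedure section says of consenting therapists that "they will be block randomized by the coordinating site (by OT or PT discipline"). Children are not randomised individually; they take the arm of their therapist.

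**The concern.** Three features of the stated rule are weak.

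- **The adjusted model is open until the data are seen.** An open list with an undefined entry condition allows more than one adjusted primary result. The reader could not tell which one was planned.
- **Factors of the design are not used to adjust the primary contrast.** Discipline restricts the randomisation but is not in the stated model. GMFCS strata cannot act at allocation, because children follow their therapist, so they can help only in the analysis. There they appear only for effect modification.
- **The form of adjustment is not stated.** In a model that has the baseline visit as a response, a covariate entered only as a main effect does nothing to the group × time contrast. The team could believe it had adjusted when it had not.

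The inclusion criteria admit children from 12 months to 5 years 11 months and GMFCS levels I to V, so expected gain over six months may well differ between children. Families consent after therapists are randomised, so the arms may also differ at baseline. Precision, and protection against chance imbalance, are at stake.

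**Working it through.** **Inputs from the Sample size section.** The section "used a two -sided α-value of 0.05, with power of 80"%. "The within-child standard deviation for change on the PEDI scale was set at 7". The authors "projected an estimated difference in the change scores between the treatment groups of 3 points on the PEDI". "We took the average cluster (number of children per therapist) size to be 3"; with ICC 0.1 the design effect is 1 + (3 − 1) × 0.1 = 1.2.

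**The plan's own figure.** n = 2 × [7 × (1.960 + 0.842)/3]² = 85.5, rounded up to 86. Then 86 × 1.2 = 103.2, rounded up to 104 per group. The stated 104 reproduces.

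**Power at 105 per group, unadjusted.** SE = 7 × √(2 × 1.2/105) = 1.058. Power = Φ(3/1.058 − 1.96) = 80.9%. With a t distribution on 70 − 2 = 68 therapist degrees of freedom it is 79.8%.

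**Main effects in the three-visit model.** Let child i have outcome Y(i,t) = group × time mean + βx(i) + error, with x(i) constant over time. The change from baseline is Y(i,6) − Y(i,0), and βx(i) cancels. With complete data the group × time contrast compares these changes, so β has no influence on it. A covariate × time term does not cancel, and neither does a covariate in a regression of change or of the follow-up score.

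**Gain if the covariates explain a share R² of the variance of change.** R² is an assumption, and the design effect is held at 1.2. Power = Φ(3/[1.058 × √(1 − R²)] − 1.96).

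| R² (assumed) | Power at 105 per group | Equivalent increase in children, 1/(1 − R²) − 1 |
|---|---|---|
| 0 | 80.9% | – |
| 0.05 | 82.9% | 5% |
| 0.10 | 84.8% | 11% |
| 0.20 | 88.7% | 25% |
| 0.30 | 92.3% | 43% |

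**Baseline PEDI alone.** With equal variances at both visits and correlation ρ, change has variance 2σ²(1 − ρ), and the baseline-adjusted follow-up has variance σ²(1 − ρ²). The ratio is (1 + ρ)/2. With the SD of change held at 7, the implied SD at one visit is 7/√[2(1 − ρ)].

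| ρ (assumed) | SD at one visit | Variance ratio | Power at 105 per group | Shift of the change-score contrast for a 3-point baseline imbalance, (1 − ρ) × 3 |
|---|---|---|---|---|
| 0.5 | 7.0 | 0.75 | 90.5% | 1.5 |
| 0.7 | 9.0 | 0.85 | 86.8% | 0.9 |
| 0.8 | 11.1 | 0.90 | 84.8% | 0.6 |
| 0.9 | 15.7 | 0.95 | 82.9% | 0.3 |
| 0.95 | 22.1 | 0.975 | 81.9% | 0.15 |

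If scores at one visit spread by about 16 to 22 points in this mixed sample (an assumption), ρ is 0.9 to 0.95. Baseline PEDI then adds 1 to 2 points of power and corrects a shift of 0.15 to 0.3 points, against a target of 3. Any larger gain would have to come from age and GMFCS predicting change.

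**The case against.** The strongest reply is that a journal article condenses the plan. A full analysis plan may name the covariates and their form, and the article's list is open, so nothing is excluded. Change-score analysis is also valid, and it matches the sample size, which is set on change. This stands as far as missing detail goes. It does not cover the conditional rule, which the article itself states and which an analysis plan that followed the article would carry over.

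A reader might infer several stronger things that the document does not support:

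- **That baseline PEDI and severity are ignored.** Baseline PEDI is a response and is subtracted in the change score. The severity interactions imply severity terms in at least a subgroup model.
- **That covariates are chosen by significance tests on the trial data.** The article names neither a test nor the data to be used. It gives no criterion at all.
- **That the planned adjustment is certain to be inert.** The cancellation holds for main effects in the three-visit model. The article says only that covariates are included, and a regression of change would use them.
- **That adjustment would remove bias from recruitment after therapists are randomised.** If the arms differ systematically at baseline, covariate adjustment is not automatically less biased than change scores, because it assumes that both arms regress to a common mean.

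One practical objection also stands. Table 1 allows child-focused children more than one therapist, so discipline is not always unique to a child in that arm.

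**Conclusion.** The point holds in a limited form. The stated primary analysis leaves adjustment to an undefined importance rule. It does not use baseline PEDI, GMFCS stratum or therapist discipline as adjusting covariates, and it does not say how covariates would enter a model in which main effects alone would have no effect on the primary contrast.

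This is a worthwhile improvement, not an error that invalidates the trial. The 104 per group reproduces and remains valid without adjustment. The size of the gain cannot be fixed from the document, which gives neither the baseline-to-follow-up correlation nor the share of variance explained. On the assumed range of R² from 5% to 30%, power at 105 per group rises from 81% to between 83% and 92%. The lower end is plausible, and baseline PEDI alone may contribute only 1 to 2 points. The firmer benefit is that the adjusted model is settled before outcomes are seen.

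**What to change.** Specify the primary model in advance:

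- outcome: PEDI at 6 and 9 months (or change from baseline at those visits);
- covariates: baseline PEDI, age, GMFCS stratum (I–II, III–V) and discipline of the randomised therapist, each allowed to differ by visit;
- therapist as a random effect;
- all four covariates kept regardless of significance, with the importance rule dropped for them.

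The handling of center can stay the team's choice; nothing here requires it to be a random effect. Co-intervention arises after randomisation and is not among the covariates proposed.

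The cost is small. Baseline PEDI, age and GMFCS level are collected on every child, and discipline is known from the randomisation. The model spends four coefficients per visit, and discipline takes one of the 68 therapist-level degrees of freedom. Discipline must be taken from the therapist whose randomisation placed the child in the arm, because child-focused children may see more than one. The analysis takes slightly more work, and the sample size does not change.

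### The switch to generalized least squares is tied to balance between the arms, but the cluster × time test of group × time depends on equal caseloads per therapist and complete visits

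*Protocol article*

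**What the plan says.** The Analyses section of the protocol article sets a mixed effects repeated measures ANOVA over the three time points. Treatment group and time are fixed, and "the clusters (therapists) will be regarded as a random factor nested within treatment groups". The group × time interaction is the primary focus, and for it "the cluster × time interaction will be used as an error term for testing significance".

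The plan expects roughly equal numbers in the two intervention groups and then adds: "if unequal sample sizes occur for some reason, generalized least squares techniques will be used for the statistical analysis". It gives no threshold for what counts as unequal, and it says nothing about unequal numbers of children per therapist.

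On caseloads, the Sample size section says "We took the average cluster (number of children per therapist) size to be 3", so 3 is an average. Under Recruitment procedure, families reply to a mailing and each child then follows the therapist into that therapist's arm. No caseload is fixed.

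**The concern.** The conditional rule watches the wrong imbalance. Testing group × time against cluster × time gives an exact F test when every therapist treats the same number of children and every child has every visit. If those conditions hold, unequal arm totals do no damage. If caseloads differ, the two mean squares no longer have the same expectation under the null, even when the arm totals match perfectly. Read naturally, the rule leaves the ANOVA where it is still valid and keeps it where it is not.

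Two further points follow from how the plan is written:

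- **Missing visits.** A classical repeated measures ANOVA discards a child with any missing assessment. That fits poorly with the intention-to-treat statement in the same section, which keeps dropouts whose outcome data can be collected.
- **The GLS branch.** Once GLS is used, the fitted covariance determines the standard error. The text names therapist and cluster × time but does not write out how repeated measurements on one child are correlated.

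At stake are the type I error of the primary test and, conditionally, its standard error.

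**Working it through.** **1. The plan's own figure.** Inputs from the Sample size section: "difference in the change scores between the treatment groups of 3 points on the PEDI"; "The within-child standard deviation for change on the PEDI scale was set at 7"; "We took the average cluster (number of children per therapist) size to be 3, the ICC to be 0.1"; two-sided α of 0.05; 80% power.

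- Unclustered n per group = 2 × (1.96 + 0.84)² × 7² / 3² = 85.5, rounded up to 86.
- Design effect = 1 + (3 − 1) × 0.1 = 1.2.
- 86 × 1.2 = 103.2, rounded up to 104.

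This reproduces the stated 104 per group. Power at 105 per group is 0.81.

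**2. Caseloads cannot all be equal at the target.** With 35 therapists per group, 220 / 70 = 3.14 children per therapist, which is not a whole number. Self-selected enrolment and dropout add to the spread.

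**3. What unequal caseloads do to the F test.** Take the baseline-to-6-month change, 105 children and 35 therapists per arm, and the same caseload distribution in both arms. The change variance is 49. The therapist part is σc² = 49 × ICC and the rest is σe² = 49 × (1 − ICC). Under the null:

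- E[MS group × time] = σe² + a σc², with a = 3(1 + CV²)
- E[MS cluster × time] = σe² + b σc², with b = (210 − 2a)/68
- Approximate type I error = P(|t68| > 1.995/√R), where R is the ratio of these two expectations

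The caseload CV is not in the document and is an assumption, shown as a range.

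| ICC | Caseload CV | a | b | R | Type I, formula | Type I, 20,000 simulated trials |
|---|---|---|---|---|---|---|
| 0.1 | 0 | 3.00 | 3.00 | 1.00 | 5.0% | 5.2% |
| 0.1 | 0.55 | 3.91 | 2.97 | 1.08 | 5.9% | 5.9% |
| 0.1 | 0.70 | 4.47 | 2.96 | 1.13 | 6.4% | not run |
| 0.1 | 0.89 | 5.38 | 2.93 | 1.21 | 7.4% | 7.4% |
| 0.3 | 0.89 | 5.38 | 2.93 | 1.46 | 10.4% | 10.5% |

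Other simulations at ICC 0.1 with CVs of about 0.5 to 0.7 gave 5.2% to 6.3%.

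**4. Unequal arms with equal caseloads.** With 75 v 135 children and 3 per therapist, a = b = 3 and R = 1. Simulated type I error was 5.0% at ICC 0.1 and 4.8% at ICC 0.3. This is the case in which the rule abandons the ANOVA.

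**5. Power of the size-weighted ANOVA (ICC 0.1, difference 3).** Simulated power was 79.9% at equal caseloads, 79.1% at CV 0.55 and 78.3% at CV 0.89. The last two are helped slightly by the inflated type I error.

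**6. GLS without a within-child term.** The cross-sectional PEDI SD is not in the document; 10, 15 and 20 are assumed.

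- Correct SE of the 6-month contrast = √(2 × 49 × 1.2 / 105) = 1.06.
- SE with therapist terms only, with 10% of the variance assigned to therapists, ≈ √(4 × 0.9 × SD² / 105) = 1.85, 2.78 and 3.70.
- Ratios: 1.75, 2.62 and 3.50.

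In 150 simulated REML fits at SD 15 with equal caseloads, the mean SE was 2.54 without a child effect and 1.07 with it, against an empirical SD of 1.00. Power was about 3% without the child effect and about 81% with it.

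**7. The ANOVA branch.** With complete data the child main effect cancels from each child's change, so step 6 does not apply there.

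**The case against.** The case for leaving the plan alone has real weight.

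- **The damage in the ANOVA branch is small.** This stands. At the plan's ICC the excess is about one percentage point of type I error for moderate variation in caseload, and power barely moves. A reader might infer a marked loss of power from unequal caseloads. That would apply to an unweighted comparison of therapist means, which the plan does not name.
- **The model is labelled repeated measures and concerns change.** The sample size uses the SD of within-child change, and a condensed article may leave the covariance to a fuller document. This also stands. A reader might infer that the plan omits the child effect and that power in the GLS branch collapses. The text does not establish that. Step 6 describes one way of fitting the words as written, not what the sponsor will do.
- **The clause on unequal sample sizes could be read to cover caseloads, or any difference between arms.** In that case GLS would nearly always apply, which is close to the remedy proposed here. This softens the point but does not remove it: the conditional rule then serves little purpose, and the unwritten covariance governs the primary result.
- **The choice depends on sample sizes, not on outcomes.** Correct. A reader might see room to choose the method by its result, and the trigger does not allow that directly. What remains is that no threshold is stated.
- **A mixed effects model need not drop children with a missing visit.** True if it is fitted by likelihood or GLS. The loss of children applies only if the ANOVA branch is run in its classical form.

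**Conclusion.** The point holds as a mis-aimed rule with modest consequences, and the wording should be changed. The trigger refers to arm totals, while the validity of the named test turns on children per therapist and complete visits. If arms are treated as balanced and caseloads vary, type I error is about 5–6% at ICC 0.1 and CV 0.5–0.7, about 7% at CV 0.9, and about 10% at CV 0.9 with ICC 0.3, with little loss of power for the size-weighted test.

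The 1.75- to 3.5-fold overstatement of the standard error is a conditional risk only. It arises if the GLS branch is fitted with therapist terms and no within-child covariance.

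These sizes rest on assumed caseload CVs, assumed cross-sectional PEDI SDs of 10–20, the plan's SD of change of 7, and a baseline-to-6-month contrast with the same caseload pattern in both arms.

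**What to change.** Delete the conditional GLS sentence and specify one REML linear mixed model, used whatever the balance between arms or therapists:

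- fixed effects for group, time and group × time;
- random therapist (nested in group) and therapist × time;
- a child random effect or an unstructured within-child covariance, stated explicitly;
- Kenward-Roger or Satterthwaite degrees of freedom;
- all children with any assessment retained.

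This removes the need for a trigger or threshold, allows for unequal caseloads, keeps children with a missed visit, and settles the covariance question. The cost is slightly more model specification, in standard software. Nothing in recruitment, treatment or assessment changes.

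### Testing group × time over three visits against a single cluster × time error term assumes the 0–6, 0–9 and 6–9 month changes are equally variable, which this design makes doubtful

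*Protocol article*

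**What the plan says.** The Analyses section of the protocol article names as primary the between-group differences in change from baseline to 6 months and from baseline to the follow-up three months later. It then states: "A combined analysis for the 3 time points will use a mixed effects repeated measures analysis of variance (ANOVA) linear model". Group and time are fixed, and therapists are random within group. The main focus is the group × time interaction, "for which the cluster × time interaction will be used as an error term for testing significance".

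On reporting, the same section says: "Results will be presented in terms of the estimated mean difference in change between the treatment groups, together with 95% confidence intervals". It does not say which standard error those intervals use. Generalized least squares is mentioned only for the case of unequal sample sizes, and no covariance structure is named for it. No sphericity correction appears.

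The Sample size section gives one SD for change, not one per interval: "The within-child standard deviation for change on the PEDI scale was set at 7".

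**The concern.** A repeated measures ANOVA over three visits has one cluster × time mean square. It estimates the average of the three pairwise change variances (at therapist level) and applies that average to every contrast. The resulting F test has its nominal level only under sphericity, that is, when the 0–6, 0–9 and 6–9 month changes are equally variable.

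The article's own facts make this doubtful:

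- The gaps between visits are 6, 9 and 3 months.
- Study treatment covers only the first 6 months, after which all children return to regular therapy (Study treatments).
- The children are 12 months to 5 years 11 months old and span GMFCS levels I–V (Inclusion criteria), so their rates of change will differ.

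Equal variances would require change over three months after the study treatment to be as variable as change over nine months that include it.

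At stake are the level of the primary interaction test and, depending on how the intervals are built, the coverage of the 0–9 month interval. That interval would carry any claim that gains persist. A child-level random intercept would not cure this, because it cancels from every change and leaves the equal-variance assumption in place.

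**Working it through.** **Inputs from the Sample size section.** The planned effect is a "difference in the change scores between the treatment groups of 3 points on the PEDI" and the SD of change is 7. On clustering: "We took the average cluster (number of children per therapist) size to be 3, the ICC to be 0.1". There are 35 therapists, hence 105 children, per group. Alpha is 0.05 two-sided and power 80%.

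**The plan's own figure.** n = 2 × [7 × (1.960 + 0.842)/3]² = 85.47, rounded up to 86. The design effect is 1 + (3 − 1) × 0.1 = 1.2, and 86 × 1.2 = 103.2, rounded up to 104 per group, as stated. Power at 105 per group is 80.9%. This rests on a single change score, so the point below does not alter it.

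**What the pooled term does.** Let S be the covariance of a child's three scores, with ICC 0.1 taken to apply to every change (an assumption). A therapist mean over 3 children then has covariance 0.1S + 0.9S/3 = 0.4S. The standard error of a between-group difference in change with variance V is √(2 × 0.4V/35). The pooled term replaces V by the mean of the three change variances, so

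pooled SE / true SE = √(mean of the three variances / own variance).

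**Assumed patterns.** The 0–6 month SD is held at the plan's 7. The other SDs are not in the article and are assumptions.

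| Pattern | Variances 0–6 / 0–9 / 6–9 (SDs) | Mean | SE ratio 0–6 | SE ratio 0–9 |
|---|---|---|---|---|
| Equal | 49 / 49 / 49 (7.0 / 7.0 / 7.0) | 49 | 1.000 | 1.000 |
| (a) Proportional to time | 49 / 73.5 / 24.5 (7.0 / 8.6 / 4.9) | 49 | 1.000 | √(49/73.5) = 0.816 |
| (b) Half measurement error, half proportional to time | 49 / 61.25 / 36.75 (7.0 / 7.8 / 6.1) | 49 | 1.000 | √(49/61.25) = 0.894 |
| (c) Scores settle after treatment | 49 / 55 / 16 (7.0 / 7.4 / 4.0) | 40 | √(40/49) = 0.904 | √(40/55) = 0.853 |
| Worst case: pure random slopes | 49 / 110.25 / 12.25 (7.0 / 10.5 / 3.5) | 57.17 | 1.080 | √(57.17/110.25) = 0.720 |

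As an example, in (a) the pooled SE is √(0.8 × 49/35) = 1.06 PEDI points. The true 0–9 month SE is √(0.8 × 73.5/35) = 1.30.

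**Simulated operating characteristics.** Balanced 35 × 3 per arm, no treatment effect, at least 40,000 trials per pattern. The F test has 2 and 136 df, and the intervals are built from the pooled mean square.

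| Pattern | F test rejects | 0–6 coverage | 0–9 coverage |
|---|---|---|---|
| Equal | 5.0% | 95% | 95% |
| (a) | 6.2% | 95% | 89% |
| (b) | 5.1% | 95% | 92% |
| (c) | 6.2–6.5% | 92–93% | 91% |
| Worst case | 8.4% | 96% | 84% |

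Two further patterns bound the picture. If scores change to 6 months and then plateau (SDs 7.0 / 7.0 / 3.8), both intervals cover about 91% and the F test rejects 6.5%. If the 6–9 month change is the most variable (SDs 7.0 / 12.1 / 15.7), the 0–9 month interval is correct (95.0%), the 0–6 month interval is far too wide (99.9%), and the F test rejects 7.1%.

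A Greenhouse–Geisser correction or an unstructured (multivariate) test brings the group × time test to about 5% in every pattern. With its own therapist-level error on 68 df, each change interval covers 95%.

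**The case against.** **The article ties the pooled term to the test, not to the intervals.** This stands. The sentence on intervals names no standard error. Naming cluster × time may be meant mainly to put the error at therapist rather than child level, which for a single change is compatible with a contrast-specific error. The coverage figures therefore hold only if the intervals use the pooled term.

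**Separate change-score analyses may already be intended.** The sentence naming the differences in change as primary comes before the combined model and can be read as two separate comparisons. That is possible, but the text gives those comparisons no error term of their own, and the only significance test it specifies is the pooled interaction.

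**No variance by interval is given, so the direction is assumed.** This also stands. A reader might infer that unequal spacing by itself invalidates the test, or that the primary p-values and the 0–9 month interval are simply wrong. The article does not support either inference. Equal change variances are possible with unequal spacing, and then everything is nominal. One pattern above also leaves the 0–9 month interval correct.

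**Generalized least squares could carry a non-spherical covariance.** It could, and exact balance is unlikely. But the stated trigger is unequal sample sizes, not unequal variances, and no structure is named.

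**Such detail may sit in an analysis plan that is not shown.** A missing correction alone would be no finding. Here the article itself names the error term, and that term is right only in a special case.

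**Conclusion.** The point holds in conditional form. The single cluster × time error term assumes equal variance of the 0–6, 0–9 and 6–9 month changes, and the design gives reason to doubt this.

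- **If equality fails,** the uncorrected F test is mildly liberal: about 5% to 6.5% in patterns (a) to (c), and about 8% in the worst case.
- **If, in addition, the intervals use the pooled term and variance of change grows with the interval,** the 0–9 month interval is too narrow, with about 89% to 92% coverage for assumed 0–9 month SDs of 7.4 to 8.6. This is the larger effect.
- **The 0–6 month interval** is about right in most patterns. Settling or a plateau after treatment makes it somewhat too narrow.

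These sizes rest on the assumed SDs, a common ICC of 0.1 for all changes, exact balance at 35 × 3 per arm, and no treatment effect. The documents do not show that the reported results will be wrong; they fix an error term that needs an assumption the plan neither states nor protects against.

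**What to change.** In the Analyses section, replace the single cluster × time error term by one of the following, and state which standard error the 95% intervals use.

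1. **Simplest:** estimate and test the 0–6 and the 0–9 month differences in change each with its own therapist-level error, on about 68 df (2 × 35 − 2).
2. **Model-based:** fit a mixed model with an unstructured within-child covariance over the three visits and therapist random effects by visit, with small-sample degrees of freedom and a stated simplification if it does not converge.
3. **If the 2-df interaction F test is kept:** apply a Greenhouse–Geisser correction. This repairs the test only, so the intervals still need contrast-specific errors.

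**Cost.** This changes analysis wording only: no new data, and the 104 per group is unaffected. Option 1 moves the critical t from 1.978 (136 df) to 1.995 (68 df). Since 1.995/1.978 = 1.009, intervals are under 1% wider where variances are in fact equal. Option 2 needs up to 6 + 6 = 12 variance parameters with about 3 children per therapist, so there is some risk of convergence or boundary problems.
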